## Abstract

**Background:**

In Nigeria, similar to many leprosy-endemic countries, leprosy is highly stigmatized. High levels of stigma among community members as well as internalized stigma among persons affected by leprosy often result in negative psychosocial consequences for those affected. To break this vicious cycle, it is important to conduct context-specific behavioral change activities. Although written material has been successful in improving knowledge and perception, it is not suitable for populations with low educational levels. Audio-delivered interventions are likely to be more suitable for people who are illiterate. This study proposes to assess the impact of an audio-delivered intervention on the perception (knowledge, attitudes, and beliefs) of community members with regard to leprosy in Nigeria.

**Objective:**

This study aims to assess the impact of audio-delivered and written health education on the perception of leprosy. Specific objectives are to (1) investigate the perception (local beliefs, knowledge, and attitudes) of community members toward leprosy and persons affected by leprosy; (2) investigate whether there is a difference in impact on perception between participants who have received audio-delivered health education and those who have received written health education, with specific reference to gender differences and differences between rural and urban areas; and (3) assess the impact of the participatory development of the audio-delivered and written interventions on empowerment and internalized stigma of persons affected by leprosy who developed the interventions. Additionally, we will translate and cross-culturally validate 4 study instruments measuring outcomes in 2 major Nigerian languages.

**Methods:**

We will use a mixed methods, cross-sectional study design for the intervention development and a 3-arm cluster randomized controlled trial for its implementation and evaluation, comprising (1) baseline assessments of knowledge, attitudes, perceptions, and fears of community members, to develop the audio-delivered content and written material, and the self-esteem and internalized stigma of persons affected by leprosy; and (2) participatory development of the audio-delivered content and written material by persons affected by leprosy and the pilot and implementation of the interventions. This will be done among different groups (selected using cluster randomization) that will be compared (control group, audio-intervention group, and written material group) to evaluate the intervention and the impact of developing the intervention on the persons affected.

**Results:**

This study was funded in June 2022, and community member participant recruitment started in January 2023. Baseline data collection was completed by May 2023 (n=811). Participatory cocreation of the audio and written health education content began in July 2023, and the materials are currently under development. Study results are expected in September 2024.

**Conclusions:**

Study findings will contribute to developing evidence-based, context-specific behavioral change interventions, which are critical to addressing stigma in many leprosy-endemic communities where leprosy is highly stigmatized, and contribute toward global triple zero leprosy efforts.

**Trial Registration:**

Pan African Clinical Trial Registry PACTR202205543939385; https://pactr.samrc.ac.za/TrialDisplay.aspx?TrialID=23667

**International Registered Report Identifier (IRRID):**

DERR1-10.2196/53130

## Introduction

### Overview

Leprosy is an infectious disease caused by *Mycobacterium leprae* [1]. Leprosy has been stigmatized since ancient times [2]. Stigma refers to a negative social response from one group toward a low-power, stigmatized group [3]. Stigma is “a social process, experienced or anticipated, characterized by exclusion, rejection, blame, or devaluation that results from experience, perception, or reasonable anticipation of an adverse social judgment about a person or group” [4]. Stigma can occur at different levels, for example, at the intrapersonal, interpersonal, community, institutional, and structural levels [5]. Many people affected by leprosy experience the negative consequences of their condition [6,7]. Stigma can have a very negative effect on employment and education opportunities, social interaction, housing, and access to health care [8]. Stigma can also indirectly cause stress and negatively impact mental well-being, quality of life, and physical health [8]. Stigma can delay seeking treatment [9] and can also impede adherence to treatment [10]. Family members and friends may experience courtesy stigma (stigma by association) [11,12].

Perception, which refers to how individuals or groups “see” an object, person, event, or institution [13-15], is an important driver of stigma [4]. The origin of stigma lies in public perceptions about people who are stigmatized. Perception comprises knowledge, beliefs, and attitudes, which are in turn influenced by personal factors (eg, personality and experience) and environmental factors (eg, culture and religion) [13,14]. Leprosy-related stigma is mainly caused by fears of contagion, external manifestations, and disabilities; religious and cultural beliefs; misconceptions; and a lack of knowledge [2,16]. Personal characteristics such as age, gender, occupation, education, and living area have also been associated with leprosy-related community stigma [17-20]. Stigma reduction (which often consists of positively influencing the perception of leprosy and increasing knowledge of leprosy) is crucial to improving the lives of people affected by leprosy and to improving leprosy services. Several interventions have successfully reduced leprosy-related stigma [21-24]. Interventions that are culture-specific and contextualized tend to be more effective [25,26].

Nigeria is among 23 global priority countries identified by the World Health Organization (WHO). In 2019, a total of 2424 new patients with leprosy were detected in Nigeria, 15% of whom had Grade 2 disabilities (G2Ds) [27]. Nigeria is among the few countries that reported more cases of G2Ds in 2019 than in previous years [27]. G2D among new patients is used as an indicator of late detection of leprosy. In addition, G2Ds (visible impairments) often exacerbate stigma and discrimination [28,29]. Leprosy is a stigmatized disease in Nigeria [30,31]. In a study among persons affected by leprosy and community members in Western Nigeria, the stigmatization of leprosy was mainly linked to perceived infectivity and perceived immoral behavior [31].

Despite progress in the control of leprosy in the last decades, the disease remains highly stigmatized [7], especially in Nigeria [30,31]. High levels of community stigma as well as internalized stigma among persons affected by leprosy may result in delayed diagnosis and disabilities [32]. To break this vicious cycle, it is important that context-specific attitude and behavior change activities are carried out. From other studies, we know that changing perceptions and improving knowledge can lead to behavior change [18,33,34]. For example, between March and June 2020, several printed materials that aimed to improve the perception of leprosy and increase knowledge about leprosy were evaluated in Uttar Pradesh, India. These context-specific materials were developed as part of NLR International’s Post-Exposure Prophylaxis project. Analysis revealed an association between the number of posters seen and a positive change in knowledge and stigma scores [35].

Access to appropriate health information is an essential step in the fight against stigma and discrimination. However, written materials are not suitable for populations with low educational levels [36]. To make health information accessible to people who are illiterate in many leprosy-endemic communities of the global south (especially women and girls), it is important to provide information through modalities other than printed materials. It is believed that audio-delivered interventions would be more suitable for people who are illiterate and low-literate. Audio-delivered interventions, for example, radio, have been shown to be successful for different stigmatized conditions such as HIV, leprosy, and albinism [37-39].

This study aims to assess the impact of an audio-delivered intervention on the perception (knowledge, beliefs, and attitudes) of community members regarding leprosy by comparing an audio-delivered intervention with written health education. The study will be conducted in Nigeria.

### Primary and Secondary Objectives

Our primary objective is to assess the impact of audio-delivered and written health education on the perception of leprosy in Nigeria. Additionally this study has the following secondary objectives: (1) to investigate the perception (local beliefs, knowledge, and attitudes) of community members toward leprosy and persons affected by leprosy; (2) to investigate whether there is a difference in impact on perception between participants who have received audio-delivered health education and those who have received written health education, with specific reference to gender differences and differences between rural and urban areas; and (3) to assess the impact of the participatory development of the audio and written interventions on empowerment and internalized stigma of persons affected by leprosy who developed the interventions.

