A total of 25 people will be included in the participatory development of the material [41]. In each state, these will consist of 10 persons affected by leprosy and 2-3 community members. Semistructured interviews will be conducted until data saturation is reached.

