### Primary and Secondary End Points

The outputs of this study will be an audio-delivered intervention and written or printed health education material for education on leprosy, awareness-raising, and stigma reduction.

In addition, all 4 scales will be translated and cross-culturally validated in Nigerian Pidgin and Hausa languages as part of this study. The qualitative outcomes are knowledge and attitudes toward (persons affected by) leprosy (eg, local beliefs, fears, and misconceptions).

Outcome measures used to be assessed at baseline and follow-up are as follows:

Demographic information: to disaggregate data by gender, the “knowledge, attitudes, and practices” (KAP) measure includes a form to collect demographic information.The KAP measure, as used in a study in India [16], covers 8 main topics: early symptoms, cause, mode of transmission, treatment, prevention, curability, contagiousness when on treatment, and prevention of disabilities. The KAP is a questionnaire and has not been formally validated as a scale (nor will it be used as a scale). We will translate and pilot test the KAP measure.Community stigma, using the EMIC-CSS (used in Nigeria but not validated in Nigerian Pidgin and Hausa yet [17]).Desired social distance toward persons affected by leprosy as a proxy for attitudes and fear, using the SDS (used among persons affected by leprosy in Nigeria but not validated in Nigerian Pidgin and Hausa yet [17]).Self-esteem and internalized stigma of persons affected by leprosy, using the RSES (used in Nigeria but not validated in Nigerian Pidgin and Hausa yet) and the leprosy-adapted ISMI (used among persons affected by leprosy and used in Nigeria but not formally validated yet [17]).

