### Data Collection

#### Overview

We will use a mixed methods approach and collect qualitative data (in-depth interviews and focus group discussions [FGDs]) and quantitative data (the KAP measure, EMIC-CSS, SDS, communication needs assessment, RSES, and ISMI). We will also collect demographic information (including literacy levels) from each participant.

This study consists of the steps and phases outlined in the following subsections.

#### Step 1

None of the tools listed in step 2 have been validated in Nigerian Pidgin and Hausa yet; therefore, they will be cross-culturally validated before use. We will assess conceptual, item, semantic, operational, and measurement equivalence using a framework for cross-cultural equivalence testing based on the work of Herdman et al [43], Terwee et al [44], and Stevelink and van Brakel [45]. In addition, the interview and group discussion guides (outlined in step 2) will be pilot tested among a small sample of participants before use. The KAP measure will be translated and pilot-tested.

#### Step 2

A baseline study to assess the perceptions of community members using mixed methods will be conducted, consisting of both in-depth interviews and FGD sessions and questionnaires (KAP, EMIC-CSS, and SDS). A communication needs assessment will be conducted as part of the baseline study to determine the most appropriate mode of delivery of the audio intervention and the most appropriate duration and frequency of the audio intervention. We will also conduct a baseline study among the persons affected by leprosy group who will be involved in the development of the interventions. Self-esteem and internalized stigma will be assessed using in-depth interviews, RSES, and ISMI.

#### Step 3

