## Discussion

### Principal Considerations

In this study, we will apply mixed methods to compare the impact of audio-delivered versus written health education intervention materials and a control group without any intervention on the perception (knowledge, beliefs, and attitudes) of community members regarding leprosy. Through a participatory cocreation process, we will develop the content of the intervention materials alongside persons affected by leprosy and implement a 3-arm cluster RCT to evaluate the effect of the intervention. The effect of the cocreation process on internalized stigma among the affected persons will also be evaluated.

Developing context-specific behavioral change intervention activities is critical to addressing stigma in many leprosy-endemic communities where leprosy is highly stigmatized. The outcome of this intervention is expected to influence knowledge and, hopefully, improve the attitudes of community members toward leprosy, as well as improve self-esteem among persons affected by leprosy. In the long run, early leprosy case finding will be boosted following stigma reduction. To the best of our knowledge, this is the first study of this kind in Nigeria. The generated educational materials (both the audio and written content) are reusable products that may be adopted or used by the national program. The audio-delivered educational content will be freely available on the Audiopedia platform, licensed under Creative Commons (CC BY).

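### Secondary objective 3 claims an impact on empowerment, but only self-esteem and internalized stigma are assessed, in about 20 co-creators with no comparison group

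*Protocol article*

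**What the plan says.** The aim appears in the Abstract (Objective) and again under Primary and Secondary Objectives: "to assess the impact of the participatory development of the audio and written interventions on empowerment and internalized stigma of persons affected by leprosy".

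The measures for this group appear in three places.
- Primary and Secondary End Points lists "Self-esteem and internalized stigma of persons affected by leprosy, using the RSES", together with the leprosy-adapted ISMI.
- Data Collection, Step 2, says of the baseline: "Self-esteem and internalized stigma will be assessed using in-depth interviews, RSES, and ISMI".
- Table 1 shows the RSES and L-ISMI as the only entries for persons affected, once at baseline and once among the outcome variables.

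Step 5 repeats the baseline methods at follow-up and adds focus groups with the persons affected.

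On who is assessed, Step 2 states "We will also conduct a baseline study among the persons affected by leprosy group who will be involved in the development of the interventions". Study Duration and Sample Size Calculation gives the size: "A total of 25 people will be included in the participatory development of the material", and then "In each state, these will consist of 10 persons affected by leprosy and 2-3 community members". Participant Recruitment and Follow-Up says that selection is purposive, to cover age, gender and villages.

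The causal wording recurs. The Abstract (Methods) and Step 5 speak of the impact of developing the intervention, and Principal Considerations says: "The effect of the cocreation process on internalized stigma among the affected persons will also be evaluated".

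**The concern.** Two things do not fit together.

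First, the objective names empowerment, and the article never mentions it again after stating the objective. If the plan is followed as written, one of the two constructs in this objective has no data collected for it by name. The likely outcomes are that it goes unreported or that self-esteem is reported in its place.

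Second, *impact* and *effect* imply a comparison with what would have happened without co-creation, and no such comparison is described. The trial's control arm does not supply one, because the randomized arms are local government areas of community members, not persons affected.

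At stake is what may be concluded about co-creation, which the article presents as a result in its own right.

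**Working it through.** **Step 1. Constructs named against constructs assessed.**

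| Place in the protocol article | What it names for persons affected |
|---|---|
| Abstract, Objective; Primary and Secondary Objectives | empowerment, internalized stigma |
| Abstract, Methods (baseline) | self-esteem, internalized stigma |
| Study Duration and Sample Size Calculation (scale validation) | ISMI, RSES |
| Table 1, baseline and outcome rows | RSES, L-ISMI |
| Primary and Secondary End Points | self-esteem (RSES), internalized stigma (L-ISMI) |
| Data Collection, Step 2 | self-esteem, internalized stigma: interviews, RSES, ISMI |
| Data Collection, Step 5 | the same methods again, plus focus groups |
| Principal Considerations | internalized stigma; an expected improvement in self-esteem |

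Empowerment stands only in the first row. The set of validated scales is fixed at four (EMIC-CSS, SDS, ISMI and RSES), and the first two are for community members. The RSES is nowhere said to stand for empowerment. Step 5 describes the interviews with persons affected as giving insight into self-esteem and internalized stigma.

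**Step 2. Number of people.** The group size reproduces: 2 states × (10 + 2 to 3) = 24 to 26, in line with the stated 25. Persons affected: 2 × 10 = 20.

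**Step 3. Is there a comparator?**
- The randomized arms consist of community members.
- The 100 persons affected in the validation work have no stated follow-up or comparison role.
- The co-creators are selected purposively and compared with themselves.
- Table 1 sets their follow-up scales alongside the community outcomes, after the interventions. The interval therefore spans delivery of the materials as well as their development.

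A before-after difference thus combines any influence of co-creation with everything else that changed over that period.

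**Step 4. Precision of the describable change (illustration only).** The half-width of a 95% interval for a mean paired change, in units of the SD of the change score, is t(0.975, n−1)/√n.
- n = 20: 2.093/4.472 = 0.47.
- n = 17: 2.120/4.123 = 0.51. This assumes 15% loss, the rate that the article uses for the community trial, so 20 × 0.85 = 17.

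The article states no target precision or power for this objective. These figures show how finely a change could be described. They do not show that any requirement is missed.

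**The case against.** The strongest reply is that the article is open about what it measures. Self-esteem and internalized stigma are named repeatedly, so a reader is not misled about the data. Internalized stigma has its own scale at both time points, backed by interviews and focus groups. *Impact* may be loose language for a mixed-methods evaluation, and the matter concerns one construct of a secondary objective outside the randomized comparison.

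Much of this stands, and it rules out several stronger readings that a reader might infer.
- *That objective 3 as a whole cannot be answered.* The documents do not support this: change in internalized stigma can be described from the planned data.
- *That time, repeat interviewing and regression to the mean all push the result the same way.* Selection is on age, gender and village, not on extreme scores, and nothing in the article gives a direction for the other influences.
- *That the sample is too small.* No significance test, power target or split by state is planned for this objective, and a missing power calculation is no error in an exploratory component.

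The reply does not remove the mismatch itself. The article states both its objective and its list of measures, and they differ, so this is a contradiction on the page and not detail left to a fuller document. Open labelling of the scales also does not supply a comparison group.

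**Conclusion.** The point holds in a limited form. No measure or interview topic is tied to empowerment. Change in self-esteem and internalized stigma among about 20 co-creators can be described but not attributed to co-creation. With 20 complete pairs the 95% interval would be about ±0.47 SD of the change score, or ±0.51 SD with 17.

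This rests on two readings: that the RSES is not silently intended as an empowerment measure, and that no comparison group of persons affected exists beyond what the article describes. If either is wrong, one sentence saying so would settle that half of the point.

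The correction is worth making because it changes what may be concluded. The primary objective and the cluster-randomized comparison are unaffected.

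**What to change.** 1. In the Abstract (Objective) and in Primary and Secondary Objectives, replace *empowerment* with *self-esteem*, and replace *impact of* with *change in … among persons affected who took part in*. The objective would then read, for example: *to describe the change in self-esteem and internalized stigma among persons affected by leprosy who took part in developing the interventions*.
2. Change *impact* in the Abstract (Methods) and in Step 5, and *effect* in Principal Considerations, to match.
3. State once that this result is an exploratory, uncontrolled before-after change.
4. If empowerment is kept, say that it is a qualitative topic and add it explicitly to the follow-up interview and focus group guides. The interviews as now described do not cover it. Co-creation began in July 2023 according to the Results section, so an empowerment baseline taken before co-creation can no longer be added.

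Items 1 to 3 cost only wording, and item 4 a few added questions. The downside is a more modest claim for one secondary objective.

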## Methods

### Study Design

We will conduct a cross-sectional study (intervention development) and a 3-arm cluster randomized controlled trial (RCT; intervention implementation and evaluation). The three arms consist of (1) an intervention group who will receive the audio-delivered intervention, (2) an intervention group who will receive the written intervention (poster or flyer), and (3) a control group who will not receive any intervention.

### Study Location and Setting

The study will be carried out in 6 local government areas (LGAs), 3 each in Cross River State (Boki, Calabar-South, and Obubra) and Taraba State (Jalingo, Yorro, and Zing). The 3 LGAs per area will be selected based on similarity in terms of literacy rate and prevalence of leprosy. Cross River is located in southern Nigeria, while Taraba is in the north. The total population of the study area is 940,540, estimated from the 2006 census, with 542,494 in Cross River and 398,046 in Taraba states. Both states have been selected because of the high prevalence of leprosy and G2D.

Cross River State notified a total of 106 new cases (17% with G2D) in 2019. The most common language spoken in Cross River State is Nigerian Pidgin. Over 90% of the people living in the selected LGAs in southern Nigeria speak Nigerian Pidgin. Other languages spoken in Cross River State include Efik, Ekoi, and Yala. The illiteracy rate (those with no schooling or primary or secondary education who cannot read at all) is 12.2% and 26.4% for male and female individuals, respectively. Occupations include farming, trading, and civil service employment. About 58% of women own mobile phones, compared with 71% among men [40]. Cross River State’s poverty index is 0.146, and the poverty headcount rate is 36.3%. The case notification rate for leprosy is 2.76 per 100,000 people based on 2020 data.

Taraba is among the 15 high-burden states for leprosy in Nigeria; an average of 100 new cases were detected between 2013 and 2017, with an average of 6% and 5% of children and G2D cases, respectively. This figure is likely to be underreported, considering the significant presence of isolated populations such as nomadic pastoralists and internally displaced people in the state.

The most common language spoken in the selected LGAs in Taraba State is Hausa; 80% to 90% of the people living in the selected LGAs in Northern Nigeria speak Hausa. Other languages spoken in Taraba State include Mummuye and Fulfulde. The illiteracy rate is 30.1% and 64.9% in Taraba State for male and female individuals, respectively. Occupations in Taraba include farming, mainly crop production and cattle rearing, petty trading, and civil service employment. The majority of men (71%) own a mobile phone, while only 44.6% of women do. Taraba State’s poverty index is 0.448, and the poverty headcount rate is 87.7%. The case notification rate for leprosy is 2.30 per 100,000 people.

